#### Early Childhood Development and School Readiness

The Australian Early Development Census (AEDC) is a cross-sectional national census of all children at the time of school entry, and it has been conducted triennially since 2009 [60]. The AEDC involves classroom teachers assessing children, aged about 5 years, across 5 domains of early childhood development, associated with readiness for school learning, namely physical health and well-being, social competence, emotional maturity, language and cognitive skills (school based), and communication skills and general knowledge. The score for an AEDC domain is marked on a scale of 0 to 10, with higher scores indicating higher levels of development. A score falling below the 10th percentile of the national AEDC population indicates a *developmentally vulnerable* result on that domain [61].

Data on the outcomes of early childhood development will be accessed from the AEDC dataset, one of the linked administrative datasets used in this study. The AEDC data available for this study contain data from the censuses held in 2009, 2012, and 2015. The first type of outcome variables is directly available in the AEDC dataset and are the dichotomous results of developmental vulnerability for individual domains and the summary measure of *being developmentally vulnerable on two or more domains* (DV2). Children assessed as vulnerable on 2 or more domains are considered to be at higher developmental risk, and they generally require additional support to progress through early schooling.

The second type of outcome variables is the domain scores, which are continuous variables. These outcome measures will be used because of the fact that a high proportion of children in our study cohort have been assessed as *vulnerable*, using the dichotomous outcome variables [61], and the use of continuous domain scores is anticipated to be more sensitive in detecting differences among groups. We will use the scores for individual domains in domain-specific analysis and the sum of the scores of the 5 domains as a general indicator of children’s overall readiness for school learning.

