#### Youth Offending

The Youth Justice dataset was provided by the NT Department of the Attorney-General and Justice, and this contains records of youth offending in the NT. The outcome measure for this study will be the cumulative incidence of first episode of a proven guilty offence within the youth justice system. The starting point for follow-up will be the 10th birthday, which is the minimum legal age of criminal responsibility, and the follow-up time will be calculated to the date of first offence or censored at the date of death, the last observed date in the linked datasets, or the set endpoint for follow-up of this study. Data are available for the period 1997 to 2017.

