### Statistical Analysis Plan

For each component study, statistical analyses will start with descriptive statistics to examine the distribution of key demographic, control, predictor, and outcome variables in the study cohort. The approach of complete-case analysis will be adopted in regression analysis. As this approach may lead to exclusion of participants with missing data, we will include comparisons of the study cohort and those excluded from analysis using suitable statistical methods (z-test, *t* test or chi-square analysis) to assess the differences between the 2 groups. When the groups are found to be statistically different on any number of included variables, we will include discussion of the implications of these differences on the validity of the study’s findings.

The dependent variable, HI, is structured as an ordinal variable, and we anticipate a *dose-response* relationship between the levels of HI and the outcome variables. In all regression analyses, the investigation of associations will use *normal hearing* as the reference category.

The study investigating the impact on AEDC outcomes will use logistic regression for dichotomous outcomes and linear regression on continuous ones. In the studies investigating the impact of HI on Year 1 attendance rates and NAPLAN results, multivariate linear regression models will be fitted to estimate the association between HI and the school-based outcome measures, and the models will include school-fixed effects to control for the average observed and unobserved differences in schools and students of the schools. In the studies examining the association between HI and child maltreatment and between HI and youth offending, multivariate survival analysis will be used by fitting Cox proportional hazard models.

In these component studies, a parsimonious model building strategy will be adopted in the regression modeling process. Univariate regression analysis will first be carried out to select variables with *P* value<.25. These and all possible 2-way interaction terms will be fitted in the multivariate regression model–building process. Variables deemed to be key confounders or moderators selected on the basis of past studies will be retained throughout the model-building process.

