The final part of the study will investigate the interplay of key early childhood factors known to be associated with youth offending. It will examine how and to what extent the outcome of youth offending in NT Aboriginal children is shaped by the health, developmental, educational, and social factors investigated in this study, including HI, AEDC outcomes, Year 1 attendance rates, Year 3 NAPLAN results, and child maltreatment. The analysis will also examine the influence from key demographic factors relevant to children’s family and school learning circumstances. Structural equation modeling (SEM), using path analysis methods, will be utilized to quantify the relative impact of these factors on the outcome of youth offending. Distributional assumptions will be assessed to identify any outliners. The model will examine the direct pathway through which HI is associated with youth offending; it will also include the indirect pathways by which AEDC outcomes, Year 1 school attendance, and Year 3 NAPLAN results act as mediators in the direct pathway. In the SEM analysis, the *maximum likelihood with missing values* convergence method will be used to relax the requirement for each child to have complete data, as it is expected that the number of children will be reduced after linking multiple datasets. Relevant model fit indices will be reported for each pathway, including *P* value, model chi-square, goodness of fit index, p of close fit, comparative fit index, the root-mean-squared error of approximation, and the standardized root mean square residual. All statistical analyses will be performed using Stata for Windows, Version 15 (StataCorp).

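### The youth-offending path model makes no provision for censoring or unequal time at risk, so its AEDC path rests almost wholly on the 2009 census cohort, followed to about age 13 to 14

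*Protocol article*

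**What the plan says.** Under Youth Offending, the outcome is the first proven offence. "The starting point for follow-up will be the 10th birthday, which is the minimum legal age of criminal responsibility". On when time at risk stops, the section says that "the follow-up time will be calculated to the date of first offence or censored at the date of death", with the last observed date or a set endpoint as further censoring dates. On the data window: "Data are available for the period 1997 to 2017". For the component study of this outcome, the Statistical Analysis Plan section says "multivariate survival analysis will be used by fitting Cox proportional hazard models".

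The last part of the same section turns to a structural equation model of offending. Its factors are hearing impairment (HI), AEDC, Year 1 attendance, Year 3 NAPLAN and child maltreatment. It has a direct path from HI, and "it will also include the indirect pathways by which AEDC outcomes, Year 1 school attendance, and Year 3 NAPLAN results act as mediators". The estimator is maximum likelihood with missing values; this "convergence method will be used to relax the requirement for each child to have complete data". The reason given is that linkage across datasets will reduce the number of children. The fit measures include the model chi-square, GFI, CFI, RMSEA and SRMR.

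On the AEDC mediator, Early Childhood Development and School Readiness says "The AEDC involves classroom teachers assessing children, aged about 5 years, across 5 domains of early childhood development" and "The AEDC data available for this study contain data from the censuses held in 2009, 2012, and 2015".

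**The concern.** The same outcome is a censored event time in one part of the plan and an ordinary endogenous variable in another. The estimator and fit indices named for the path model belong to a linear covariance-structure model. Such a model can fill in a missing mediator under its assumptions, but it has no likelihood contribution for a child who has not offended yet because follow-up was short.

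This matters because birth year fixes two things at once: whether a child can have an AEDC record, and how long offending can be observed. The youngest AEDC children have not reached age 10 when the data end. The children with the longest offending follow-up started school before the first census. The section treats the shortfall only as incomplete linked data.

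At stake is the stated purpose of this part, which is to compare how much each early-childhood factor contributes to offending. An AEDC path that looks weak could reflect calendar time rather than child development.

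**Working it through.** The article gives no sample size, event count or power for the path model, so there is no planned figure to reproduce. The check is date arithmetic.

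**Inputs from the article.** AEDC census years 2009, 2012 and 2015; age at census about 5; risk starts at the 10th birthday; offending data end in 2017.

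**Assumptions.** The data run to 31 December 2017 (2018.0), the latest possible date. Base case: mid-year census and age exactly 5. Range: age 4.5 to 6.0 and census at about April, July or August.

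**Formula.** 10th birthday = census date − age at census + 10. Time at risk = max(0, 2018.0 − 10th birthday).

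| AEDC census | 10th birthday (base) | Time at risk (base) | Range | Age at end of 2017 (range) |
|---|---|---|---|---|
| 2009 | 2009.5 − 5 + 10 = 2014.5 | 3.5 years | 2.9 to 4.7 | 12.9 to 14.7 |
| 2012 | 2012.5 − 5 + 10 = 2017.5 | 0.5 years | 0 to 1.7 | 9.9 to 11.7 |
| 2015 | 2015.5 − 5 + 10 = 2020.5 | 0 | 0 throughout | 6.9 to 8.7 |

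**Share of person-time.** Assume equal cohorts, a mid-year census and age spread evenly over 4.5 to 6.0. Mean time at risk is then 3.75, 0.75 and 0 years. The 2009 cohort supplies 3.75/4.50 = 83%, the 2012 cohort 17% and the 2015 cohort none.

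**The other mediators.** By calendar year:
- Year 3 NAPLAN in 2008 at age 8 means birth in 2000, age 10 in 2010 and about 7 years at risk.
- Year 1 attendance in 2005 at age 6 to 7 means birth in 1998 to 1999, age 10 in 2008 to 2009 and about 8 to 9 years.
- The latest groups have no time at risk. NAPLAN 2016 means birth in 2008 and age 10 in 2018. Attendance in 2016 means age 10 in 2019 to 2020.

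These two mediators therefore reach well beyond AEDC, but they also need a restriction at the recent end.

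**What unequal follow-up alone does.** With an assumed constant hazard h per year, the proportion with an offence by the end of 2017 is 1 − exp(−h·t). At h = 0.02, t = 3.5, 0.5 and 0 give 6.8%, 1.0% and 0%; an assumed 8-year window (age 10 to 18) gives 14.8%. At h = 0.01 the four values are 3.4%, 0.5%, 0% and 7.7%; at h = 0.04 they are 13.1%, 2.0%, 0% and 27.4%. The cohorts differ through calendar time only.

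**Illustrative simulation.** Offending was coded yes/no by the end of 2017 and regressed linearly on AEDC score. Assumptions: equal cohorts, 10% to 30% cumulative risk over ages 10 to 18, hazard ratio 1.5 per SD of AEDC score, and a flat or rising Weibull hazard (shape 1, or 2 and 3). Coefficients are relative to their age-10-to-18 value.

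| Analysis | Flat hazard | Rising hazard |
|---|---|---|
| All three cohorts, children not yet at risk coded as non-offenders | 20% to 24% | 4% to 11% |
| 2009 cohort only | 51% to 58% | 13% to 30% |

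The second row is the effect of a short window: a smaller risk difference at younger ages, not a coding error. The further drop to the first row comes from the added cohorts. With 10% risk and a flat hazard, the 2009 coefficient is 0.0202 and the pooled one 0.0081, a ratio of 0.40; across all scenarios this ratio is about 0.33 to 0.41.

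**The case against.** The strongest reply is that a journal article condenses a fuller plan. Eligible birth cohorts, the coding of offending and a common age horizon may be set there. The Study Cohort section says that eligibility will vary by component, and Youth Offending allows a set endpoint. This stands in part: the coding is not stated, so nobody can say that children under 10 will be entered as non-offenders. The reply does not remove the point, because the article does fix the estimator, the fit indices and the data windows, and these do not fit a censored outcome.

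Second, a triennial census makes AEDC availability depend largely on birth year. Missingness that depends on an observed variable can be missing at random if that variable is in the model. This stands. A reader might infer that the absence of AEDC in older children by itself invalidates the estimator; it does not. The difficulty lies in the censored outcome, and in birth year not being named in the model.

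Third, maltreatment. A reader might infer that it is left out, so that its share falls into the direct effect. The text does not support that: maltreatment is among the factors to be examined and is absent only from the sentence naming the mediators. If it enters as a predictor of offending, the direct path is already conditional on it. What remains is narrower. The Objectives hypothesise that HI raises the risk of maltreatment, yet no indirect path through it is named, so the direct/indirect split is open to more than one reading.

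Fourth, the hazards and hazard ratio above are assumed. They show direction and rough scale, not a prediction for this study.

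**Conclusion.** The point holds at moderate severity. The path model takes an outcome that the article itself treats as a censored first event and puts it under a method with no stated handling of censoring or unequal time at risk. For AEDC the dates leave about 3.5, 0.5 and 0 years at risk. The zero for 2015 and the small value for 2012 (at most 1.7 years) persist over every age and census month tried. That the method ignores censoring is inferred from the named estimator and fit indices. The size of any attenuation depends on the unstated coding.

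Two stronger readings are tempting. One is that the AEDC path cannot be estimated. It can: the 2009 cohort has roughly 3 to 4.7 years at risk, enough for an estimate confined to offending up to about age 13 to 14. The other is that the whole direct/indirect split is an artefact. The dates do not show that, since attendance and NAPLAN include groups with 7 to 9 years at risk. Nor is the hypothesis that HI is associated with offending affected, because Cox models test it.

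**What to change.** 1. Restrict the path model to children with time at risk after the 10th birthday before the data end, and state the eligible birth cohorts.
2. Model offending in one of two ways: as an offence by age X, with every included child observed to X; or with a survival or discrete-time hazard equation in a generalised structural equation model.
3. Include birth year in the model.
4. Limit the AEDC indirect effect to offending at about ages 10 to 14 in the 2009 census cohort, and say so wherever it is reported. If a fixed horizon is used, X near 13 would keep nearly all of that cohort, whose ages at the end of 2017 are 12.9 to 14.7.
5. Specify a path from HI through maltreatment to offending, using maltreatment before age 10 so that it precedes the outcome.
6. State how offending is coded.

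The cost is fewer children, a narrower claim about AEDC and some programming. A survival or discrete-time equation also gives up the linear-model fit indices, and the handling of missing mediators must be restated, because the planned missing-data likelihood belongs to the linear model. No new data are needed, and the article reports that analysis had only begun.

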## Results

The study commenced in 2018. Ethics clearance and data custodian approvals for data access and linkage have been obtained. This has enabled the completion of data linkage and the commencement of data analysis for individual component studies. Findings are expected to be submitted for publication in peer-reviewed journals in 2019 and 2020.

## Discussion

### Principal Findings

The availability of the RHA dataset for data linkage with a wide range of health, education, child protection, and youth justice datasets has provided an unprecedented opportunity for investigating the impact of HI on life-course trajectory of Aboriginal children and young people. The hearing assessment results obtained through pure tone audiometry for a large cohort of remote-dwelling Aboriginal children have enabled the direct use of HI as the predictor variable in this study, instead of using its precursor or causative condition, OM, which may introduce an unknown level of misclassification. It is expected that this study will provide the first comprehensive evidence for the impact of HI on these various measures of the life-course trajectory in the study population. Furthermore, the comparatively large sample and the use of raw test scores of AEDC and NAPLAN as continuous variables will provide a robust statistical power, which will increase the likelihood of detecting significant association with the selected outcomes. In each of the component studies, we will discuss sources of potential bias. One example is that children included in the RHA database are not a random sample of remote Aboriginal children in the NT, with a risk of selection bias. A second source of potential bias is the use of complete-case analysis. We will also discuss the likely direction of potential bias and the extent to which they may affect the validity of our results.

### Conclusions

The findings of this study will have significant implications for government departments and health and social service providers in policy development, service design, and resource allocation. The results can also be used as baseline measurements for monitoring interventions aimed at improving the ear and hearing health of Aboriginal children, as well as their developmental, educational, and social outcomes. The use of a linked administrative dataset in this study will further illustrate the utility of data linkage research methods for informing comprehensive service planning and evaluation.

## Abbreviations

AEDC: Australian Early Development Census
AOM: acute otitis media
ARIA+: Accessibility and Remoteness Index of Australia
CSOM: chronic suppurative otitis media
dB HL: decibels hearing level
HeLoKids: Hearing Loss in Kids
HI: hearing impairment
NAPLAN: National Assessment Program–Literacy and Numeracy
NT: Northern Territory
OM: otitis media
OME: otitis media with effusion
RHA: Remote Hearing Assessment
SA: South Australia
SEM: structural equation modeling
